A sample size calculation using Gpower was performed assuming that the intervention will reach a (conservative) difference of 8.8 nmol/L between the intervention and the control group (situation 3 in Table 2) at the final measurement point (at 8 weeks). This would mean that the decrease in the control group from baseline to week 8 would be -22.3 while in the intervention group this would be -13.5 (difference of 8.8 nmol/L). The sample size calculation is based on the statistical analysis conducted for the primary objective, namely the difference in serum 25(OH)D between the intervention and control group at the final measurement point, taking into account an alpha of 0.05 and a power of 0.90. The standard deviation within one group is estimated based on a previous similar study which also implemented low-dose UVB exposure to increase serum 25(OH)D in a sample of 20 healthy participants, albeit over a week period using three full-body UVB sunbed sessions [35]. In the post-measurement of this study, they found a significant increase in serum 25(OH)D of 13.9 nmol/L. One month after the end of the UVB intervention they still found a significant increase of 8.8 nmol/L, which is a similar difference we expect in the intervention group compared to the control group. The standard deviation for the power calculation was therefore based on the standard deviation on the difference score found in the sample in this study (similar sample size and similar changes in serum 25(OH)D), namely 8.4 nmol/L. The sample size for detecting a difference of 8.8 nmol/L assuming a standard deviation of 8.4 nmol/L in each group would be 17 participants in each group (see figure 3 below). As we currently only have the availability of 14 lamps, we will choose for 14 participants in each group, and aim to find a larger effect, which is not unlikely when on average, there is somewhat more than 50% desk occupancy and/or if we reach a higher exposure surface area.

[figure not shown]

**Figure 3.** Sample size calculation for change in serum 25(OH)D at 8 weeks

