**7.3.4*****Secondary parameters on sleep and general fatigue***

Participants will receive a participant ID from the researcher at the TU/e which they (the participant) will use to complete the questionnaires. The online tool Limesurvey will be used to complete the questionnaires. The questionnaires on sleep and fatigue will be completed via this tool three times (baseline, measurement 1, and measurement 2). The daily presence diary (completed daily on paper) will be uploaded (scan or photo) via Limesurvey as well every week using the same participant ID. Limesurvey is a locally installed and secured tool currently used at the TU/e for conducting online questionnaire research. Data collected via this tool will only be saved locally at the secured TU/e server. Participants will only fill in their participant number and the answers to the questionnaires. No other personal data that can be tracked back to a person (e.g. names, e-mail addresses, residence, IP numbers etc.) will be probed in these questionnaires. Limesurvey data will be downloaded at the end of the study by the independent HTI researcher who will pseudonymize the data before it is sent (together with the serum 25(OH)D values) to the researcher who will conduct the analyses ([name]).

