## 9. STATISTICAL ANALYSIS

The data analyses consist of multiple steps. All data will be presented quantitatively.

As a first step, we will inspect the distribution of the variables of interest. A Shapiro-Wilk test will be conducted to inspect normality of the variables. If needed and possible, a transformation of the scores will be performed to adhere to the assumption related to normality for the statistical analyses. Subsequently, an outlier detection will be performed with outliers determined as values more than 3 SD's from the mean.

Next, we will provide the descriptive statistics for the experimental and control condition for the variables measured only at baseline (see Table 1), as well as for the dependent variables (i.e., the variables for the primary (serum 25(OH)D) and exploratory research objectives (fatigue and sleep), see Section 2.) for each of the measurement points. Comparisons of the variables at baseline will be investigated via independent samples T-test to examine whether there were significant differences between the two groups for any of the variables at measured baseline. If the data appears to be not normally distributed and no transformation is applicable, we will employ a non-parametric test (Mann-Whitney test).

Subsequently, the main research objective (i.e., effects of the light intervention on serum 25(OH)D at week 8) will be investigated using an ANCOVA analyses with the intervention (yes/no) as predictor and change scores in serum 25(OH)D as outcome variable. This analysis will further be controlled for average desk presence and time spent outside. In case data is non-normally distributed a non-parametric test (Mann-Whitney test) will be conducted taking into account the limitation that this analysis cannot control for the mentioned confounders. Analyses will only be conducted with data from participants with both the baseline measurement and the final measurement point available. An alpha level of 0.05 will be used as criterion.

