After that, an explorative Linear Mixed Model (LMM) analysis will be conducted to examine changes in serum 25(OH)D over time (i.e., first and second measurement, using baseline scores as a control variable). LMM analyses will be executed because this type of analysis takes into account dependency of the data due to the repeated measures as well as potential missing values at any of the measurement points. In case a significant Intervention \* Measurement interaction is found ( $p < 0.05$ ), post-hoc comparisons are conducted to investigate differences between the intervention and control group at each of the two measurement points. In addition, we will conduct an exploratory LMM analysis in which we investigate the correlation between UVB dose (calculated based on desk presence and clothing) and serum 25(OH)D over time to examine whether there are large differences in these values based on the UVB dose participants received. These explorative analyses will also be controlled for time spent outside during daytime.

Last, exploratory LMM analyses will be conducted to investigate relations between the variation in serum 25(OH)D and variations in sleep duration, sleep quality, and general feelings of fatigue.

This will be established by running a LMM model with serum 25(OH)D as well as measurement point as predictor in order to account for changes in sleep patterns or fatigue levels over time. For visual inspection purposes, this will also be investigated separately in both the intervention and the control

group. This will be analyzed in this way due to a lack of blinding in participants which may create bias when directly investigating the effect of the intervention on fatigue/sleep.

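### The exploratory mixed model makes the week-4 and week-8 arm comparisons conditional on an interaction that tests only whether the arm difference changes between those two visits

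*Protocol*

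**What the plan says.** The main objective in protocol section 9 is tested by "ANCOVA analyses with the intervention (yes/no) as predictor and change scores in serum 25(OH)D as outcome variable", at week 8, with desk presence and time outside as further covariates. It is restricted to participants who have both a baseline and a final value.

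The same section then says that "an explorative Linear Mixed Model (LMM) analysis will be conducted to examine changes in serum 25(OH)D over time", and defines the data in the model as "first and second measurement, using baseline scores as a control variable". The stated reasons for a mixed model are the repeated measures and its tolerance of missing visits. The rule for comparing the arms follows: "In case a significant Intervention \* Measurement interaction is found" at p < 0.05, "post-hoc comparisons are conducted to investigate differences between the intervention and control group at each of the two measurement points". The section describes no other arm contrast from this model.

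Section 7.3.4 settles which visits are meant, because it describes the assessments as completed "three times (baseline, measurement 1, and measurement 2"). The first and second measurements are therefore weeks 4 and 8. Elsewhere the protocol counts the baseline questionnaire and blood sample as the first. That count cannot apply here, because baseline is separately assigned to the covariates.

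**The concern.** Testing an interaction first is natural when baseline is one of the outcome levels. Arm-by-time then carries the treatment effect, since the arms start together and separate. Here baseline has been moved to the covariates, and the treatment effect sits in the arm term and in the arm difference at each visit. The interaction answers a different question: does the effect at week 8 differ from the effect at week 4?

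Using that answer to decide whether the arms are compared at each visit can withhold the comparisons when the lamp works. It could also lead a reader to take a non-significant interaction as absence of a lamp effect. The introduction says this pilot is meant to inform a larger and longer study, so arm differences with intervals at both visits are among its more useful outputs.

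**Working it through.** **Inputs.** From section 4.4: planned week-8 difference 8.8 nmol/L, SD 8.4 in each group (a difference-score SD from an earlier sunbed study), alpha 0.05, power 0.90, 17 per group calculated and 14 per group used. From Table 2, effects at weeks 4 and 8: 12.4 and 17.6 (0.45 SED, 10.5% body surface); 8.8 and 13.6 (0.45, 6.5%); 6.2 and 8.8 (0.225, 10.5%, the row used for the sample size); 3.8 and 5.5 (0.225, 6.5%).

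**Assumed, because the protocol does not give them:** SD 8.4 at week 4 as well as at week 8; a within-person correlation rho between the two visits of 0.5 to 0.9; two-sided testing.

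**The plan's own figure.** A two-sample t calculation with difference 8.8, SD 8.4 and 90% power gives 17 per group with one-sided alpha 0.05, and 21 with two-sided alpha. The stated 17 therefore reproduces as a one-sided calculation; the text does not state the sidedness. The powers below are two-sided. One-sided, the week-8 comparison with 14 per group would have 85% power instead of 76%. The logic of the point does not depend on this.

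**What the interaction is.** Write D4 and D8 for the arm differences at weeks 4 and 8, adjusted for baseline. With two outcome levels, interaction = D8 − D4. If D4 = D8 = 8.8 it is zero, and the condition is met only at the 5% false-positive rate.

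**What the protocol's model predicts.** Most of the week-8 effect is already present at week 4: 12.4/17.6 = 70%, 8.8/13.6 = 65%, 6.2/8.8 = 70%, 3.8/5.5 = 69%. The interaction is what remains. In the sample-size row it is 8.8 − 6.2 = 2.6 nmol/L; in the optimal row it is 17.6 − 12.4 = 5.2.

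**Power formulas (noncentral t, 26 df, 14 per arm).**
- One visit: standard error = 8.4 × √(2/14) = 3.17. Noncentrality is 8.8/3.17 = 2.77 at week 8 (power 76%) and 6.2/3.17 = 1.95 at week 4 (power 47%).
- Interaction: SD of the within-person difference = 8.4 × √(2(1 − rho)), and standard error = that SD × √(2/14). At rho 0.7 the SD is 6.51, the standard error 2.46, the noncentrality 2.6/2.46 = 1.06 and the power 18%.

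| Row of Table 2 | Interaction (nmol/L) | Condition met, rho 0.5 / 0.7 / 0.8 / 0.9 | Week-4 power, no condition | Week-8 power, no condition |
|---|---|---|---|---|
| 0.225 SED, 10.5% (sample size) | 2.6 | 12% / 18% / 24% / 42% | 47% | 76% |
| 0.45 SED, 10.5% (optimal) | 5.2 | 35% / 53% / 70% / 94% | 96% | over 99% |
| 0.45 SED, 6.5% | 4.8 | 31% / 47% / 63% / 90% | 76% | 98.5% |
| 0.225 SED, 6.5% | 1.7 | 8% / 10% / 13% / 21% | 21% | 38.5% |

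The SD of the difference in these columns is 8.40, 6.51, 5.31 and 3.76.

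**Check by simulation.** The mixed model with baseline as covariate was fitted to 400 simulated trials per scenario at rho 0.7 (baseline mean 66.4; baseline SD 20 and a control decline of 13 by week 4 assumed). Interaction significant versus arm main effect significant: 18% versus 72% in the sample-size row; 3% versus 81% for a constant effect of 8.8; 52% versus 99.5% in the optimal row. These agree with the formulas; the 3% is compatible with a nominal 5% in 400 runs.

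**The case against.** The best defence is that the efficacy question is answered elsewhere. The primary ANCOVA tests the week-8 effect with no interaction condition. The mixed model is labelled exploratory and aimed at change over time, for which the interaction is a sensible test. This stands, and it limits the seriousness of the point. It does not rescue the rule, because what the interaction controls is the comparison of the arms at each visit, not a statement about change.

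Three stronger readings are tempting, and the protocol does not support them.

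- A reader might infer that the model yields no arm comparison at all unless the interaction is significant. The text conditions only the visit-specific comparisons. It does not forbid reporting the arm main effect, which such a model would ordinarily contain and which may be covered in an analysis plan not seen here.
- A reader might infer that week 4 is otherwise unused. Section 9 gives descriptive statistics by arm at each measurement point. It also plans mixed models for UVB dose and for sleep and fatigue that use week 4 without this condition. What is missing is another stated inferential comparison of the arms at week 4.
- A reader might infer that the condition will usually fail. That holds in the sample-size row over the whole assumed range, but not in general. In the two 0.45 SED rows at correlations of 0.8 to 0.9, the condition is met in 63% to 94% of trials. Section 4.4 says the sponsor hopes for an effect larger than the planned one.

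**Conclusion.** The condition is wrong for its purpose. With weeks 4 and 8 as outcome levels and baseline as a covariate, the interaction measures only a change in the arm difference between visits, and a constant lamp effect leaves it at zero. This follows from the model as stated and needs no assumption about size.

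The size does rest on assumptions. With SD 8.4 at both visits and a correlation of 0.5 to 0.9, the condition is met in about 12% to 42% of trials in the sample-size row, against 76% power at week 8 and 47% at week 4. In the optimal row it is met in about 35% to 94%, against 96% or more, so at the top of the correlation range little is lost there.

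The primary conclusion is not touched. The loss concerns the one stated inferential arm comparison at week 4, and the week-8 estimate that uses participants whom the primary analysis drops for lack of a final value. This is worth correcting, but it is confined to an exploratory analysis of a 28-person pilot.

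**What to change.** In section 9, remove the interaction condition. Fit arm, visit, arm-by-visit and baseline, keeping the planned adjustment for time outside. State that the arm difference with its 95% confidence interval is always reported at week 4 and at week 8 and is labelled exploratory. Use the interaction only to describe whether the effect changes between the visits, and say that a non-significant interaction is not evidence against a lamp effect.

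The cost is a rewording of one sentence. No data, participants or visits are added. The primary test and its alpha are unchanged, because these comparisons remain exploratory.

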## 6. INVESTIGATIONAL PRODUCT

### 6.1 Technical description

In order to investigate the effectivity of adding **ultra-low** dose(<0.5 SED, UVI ≈0.06), but safe (according to the IEC62471) UVB irradiance in a general office lighting solution, a special lighting research device is developed according to the general lighting guidelines with respect to photobiological safety, mechanical and electrical requirements. The newly developed luminaire is based on a released, commercially available Free Floor Standing product (<https://www.lighting.philips.com/main/prof/indoor-luminaires/free-standing/smartbalance-free-floor-standing> and D6\_5 CE declaration of commercial available smart\_balance). The standard product is modified in such a way that

- Uplight is removed
- Downlight is reduced
- UVB light is added
- Light exit window is replaced by a UVB resistant version
- Drivers are replaced in line with new led configuration
- Bluetooth control is added to set the on-off rhythm and level.
- The level can only be configured by trained people and within safe limits.

The special lighting device is designed for research purposes towards new opportunities for general lighting and will not be commercialized as is.

The newly-developed luminaire-prototype emits visible and a very low amount of invisible (UVB) irradiation exposing unprotected skin and eye, and enabling natural processes that occur when the body is exposed to daylight; Therefore special attention has been dedicated to the photobiological safety as this is seen as the major modification of the free floor standing luminaire:

- Direct view to the naked UVB LED is prevented by the diffuser and in the event the diffuser is removed from the head, the UVB LEDs go off.
- Over exposure is prevented by limitation of the maximum UVB output by a firmware setting in the driver and a real time clock automatically turns on and off the light output (30.000 s).
- The personal desk-based lighting intervention will be checked on UVB irradiance levels on a regular basis to ensure a consistent dose during the pilot study. The relative stability will be monitored by a point measurement via solar meter model 6.5 (UV) at 20 cm of the head of the luminaire. Additionally, a continuous daily dose measurement is conducted by placing wear shade dosimeters at the desk.
- Device labeling and instruction to the user to not stare in the luminaire head and to prevent prolonged exposure to distances shorter than 80 cm.

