## 6.2 Operating behavior

### *First day luminaire behavior*

After the first blood sampling has been taken place, the luminaire will be powered by putting the plug in the mains socket by the technical team. When the luminaire is connected to power it will start with dimmed white light and no UVB. A small amount of white light is emitted to indicate that the luminaire is ON. At noon or when powered after 13.00 hr, the next morning, the luminaire will switch ON (full brightness and UVB) according the preset schedule: ON at 8.50 hr and OFF at 17.10 hr (both the white and UV-B light will turn off). This behavior will also occur in case of a power cycle / disturbance in power.

*Luminaire behavior during the study*

The luminaire will automatically switch ON (full brightness and UVB) at 8.50 hr according to the preset schedule. At 17.10 hr both the white and UV-B light will turn off. This will be repeated for all days during the study period as long as the luminaire is powered. The simultaneous switching on of the visual white light and the UVB lights is an additional visual cue to the participant and other people living in the home to remind them that there is UVB irradiance and that directly looking into the luminaire should be avoided.

The luminaire is equipped with caution labels and a user manual will be supplied to the participant to facilitate proper use of the luminaire and easy access to a contact person if questions pop up.

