### 7.4.1.3 UV-dose measurements

Because the major determinant of artificial UV exposure will be time spent at desk each week and body surface exposed area, this will be recorded daily using a daily diary (see Figure 7), in which all subjects (also those in the control group) will self-report desk presence time and time spent outside in the morning and afternoon of their working day, and give an indication how much body surface areas was exposed during that day. Time spent outside during daylight in the weekend will also be reported on Monday.

Together with KNMI data we will be able to estimate the natural UVB exposure of the participant and provide for an analysis whether both groups behave similarly in their natural UVB dose. However, natural UVB exposure is expected to be minimal during the study months in autumn and winter (see [39])

Participants will gently be reminded to fill in the daily diary every day towards the end of the day. At the end of the week, they will receive a link to upload a scan or photo of the completed daily diaries or they can do this daily via a link provided at the start of the study.

|                                                  |               |              |               |              |               |              |               |              |               |              |
|--------------------------------------------------|---------------|--------------|---------------|--------------|---------------|--------------|---------------|--------------|---------------|--------------|
| Daily diary    week 1                            |               |              |               |              |               |              |               |              |               |              |
|                                                  |               |              |               |              |               |              |               |              |               |              |
| Estimated Desk Presence & Estimated Time Outside |               |              |               |              |               |              |               |              |               |              |
| Time/Day                                         | Monday        |              | Tuesday       |              | Wednesday     |              | Thursday      |              | Friday        |              |

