|                                       | malfunctioning of the luminaire     | *prolonged lifetime test did not show any malfunctioning or stability changes                                                                                                                                                                                                                                                                                                                                                                                                                                                                     | 1                     | 1        | Negligible     |
| photobiological safety                | exceeding 0.7 SED                   | *Bluetooth controller is secured via a pin-code to prevent misuse
*The max UV-B light output is limited by a firmware setting in the driver to a safe level:
-80mA
-MAX DALI level of 241
Single failure prevention of the setting is added by means of a 100mA fast fuse in the UV-B LED circuit.
*RCT clock turns the device automatically on and off
*Prototype is equipped with switch inside the luminaire head, which will switch off the UV-B LEDs in case the luminaire head is opened.
personalize dlighting device | 1                     | 1        | Negligible     |
|                                       | direct (prolonged) view to UV-B LED | *Protect installers: The prototype is equipped with a real time clock (RTC), which is setup at installation. After this setup, light will switch on at specified time stamps as agreed in the test protocol.
At power on, the luminaire will switch on at a dimmed white light level. UV-B will remain off. From next daily cycle schedule point, the light level will be set to the desired level. From that moment, the RTC will set the light in a daily cycle.                                                                             | 1                     | 1        | Negligible     |

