- Your desk has been taped to indicate the area of sufficient user's UV-B exposure. Please, try to work as much as possible in this area to receive the intended safe dose of UVB irradiation.
- Please, indicate to others in the home office, not participating the test, to be placed at a minimal distance of 1.6m to the luminaire.
- Please, unpower the device if you experience skin redness or eye strain and please report the event.
- Any damage or unexpected behavior should be reported directly

Co-workers, not participating the test, should be placed at a minimal distance of 1.6m to the luminaire.

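### The UVB dose in the exploratory dose-response model takes lamp output for granted, and the planned desk dosimeter record that could correct it is not used

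*Protocol*

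**What the plan says.** **Dose variable.** Section 9 describes an exploratory mixed model in which "we investigate the correlation between UVB dose (calculated based on desk presence and clothing) and serum 25(OH)D over time". Section 7.4.1.3 gives the reason for relying on the diary: "Because the major determinant of artificial UV exposure will be time spent at desk each week and body surface exposed area". The diary example there (Figure 7) records desk time, time outdoors and uncovered body parts. It has no entry for whether the lamp was working.

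**Lamp behaviour.** Section 6.2, repeated in section 12.1.2, says: "When the luminaire is connected to power it will start with dimmed white light and no UVB". It continues: "At noon or when powered after 13.00 hr, the next morning, the luminaire will switch ON (full brightness and UVB) according the preset schedule". It then adds: "This behavior will also occur in case of a power cycle / disturbance in power". Table 4 in section 12.1.1 puts the restart more generally: "From next daily cycle schedule point, the light level will be set to the desired level".

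**Who can cut the power.** At installation, lamp users are shown how to turn the lamp off (section 7.4). Section 12.2 tells them: "Please, unpower the device if you experience skin redness or eye strain and please report the event".

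**Output measurement.** Section 6.1 states: "Additionally, a continuous daily dose measurement is conducted by placing wear shade dosimeters at the desk". Section 12.2 repeats this and adds a weekly meter check. In both places the stated purpose is to confirm that lamp output stays steady. Neither section 7.3 (data handling) nor section 9 brings these readings into the dose variable.

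**The concern.** Desk time and UVB time are the same only if the lamp emits UVB throughout 8:50 to 17:10. The restart rule allows hours in which a participant sits under a lit lamp that gives no UVB, and the diary credits those hours in full. Some switch-offs may also be non-random, since skin redness or eye strain is a stated reason to cut the power.

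The dose model is where the plan relates 25(OH)D to the dose each person received. If the lamp shows little effect, a dose variable that cannot see lamp output cannot tell a dose that did not work from a dose that was not delivered. That distinction matters for a pilot meant to lead to a larger study.

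**Working it through.** **Inputs from the protocol.** Emission window 8:50 to 17:10; full-day dose about 0.45 SED (section 5); 1 SED = 100 J/m² (abbreviations); restart at noon, or the next morning if powered after 13.00 (section 6.2); 14 lamps; desk presence of at least 2.5 days per week for 8 weeks (section 4.2); 40 workday diaries (Table 3).

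**Reproducing the plan's own figure.** 17:10 − 8:50 = 500 min = 30,000 s, which matches section 5. Implied dose rate: 0.45 / 8.333 h = 0.054 SED per hour, or 45 J/m² / 30,000 s = 1.5 mW/m².

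**Loss on one day from a brief interruption at clock time t**

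- Before noon: 12:00 − t. The maximum is at 8:50: 190 min, 190/500 = 38%, 0.45 × 0.38 = 0.171 SED.
- After 13.00: 17:10 − t. The maximum is just after 13.00: 250 min, 250/500 = 50%, 0.45 × 0.50 = 0.225 SED.
- Between 12:00 and 13.00 section 6.2 does not say what happens. If UVB then waits until the next morning, the loss could reach 310/500 = 62%.
- Power restored before 8:50: unclear. Read with Table 4, UVB may start at 8:50 as scheduled, with nothing lost.

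A lamp left unplugged for longer loses more. In every case the diary-based dose does not change.

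**Average over the window.** Suppose a brief interruption falls at a uniformly random time. With noon as the dividing point, the mean loss is (190²/2 + 310²/2)/500 = 132 min (2.2 h). With 13:00 it is (250²/2 + 250²/2)/500 = 125 min (2.1 h). The loss is at least 1 h in 76% of cases and at least 2 h in 52%.

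**Share of the eight-week dose.** One half-day loss is 0.5/40 = 1.25% over 40 workdays, or 0.5/20 = 2.5% over 20 (2.5 days × 8 weeks).

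**Effect on the dose variable.** The protocol gives no interruption rate, so this part is illustrative. Assumptions: 14 lamp users only, desk presence uniform on 50 to 100%, exposed body surface uniform on 6.5 to 10.5%, 40 workdays, delivered dose = diary dose × (1 − fraction lost).

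| Scenario | Mean dose lost | Correlation, diary vs delivered |
|---|---|---|
| About one half-day outage per person | 1.2% | 0.9985 |
| About one 38% loss per person per week | 7.6% | 0.994 |
| 2 of 14 lose 38% every day | 5.4% | 0.83 |
| 3 of 14 lose 38% every day | 8.1% | 0.78 |

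The harm comes from losses concentrated in a few people, not from the average. The third row loses less dose overall than the second but disturbs the ranking of participants far more.

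**The case against.** The strongest case against is that the problem rests on behaviour the protocol does not describe. The lamp is installed by a technician and switches itself, and participants are told they need not operate it. A restarted lamp is visibly dim, unexpected behaviour is to be reported, switching off for redness or eye strain is to be reported, and output is metered weekly. No passage suggests daily re-powering. The model is exploratory, in a trial of 28 people, and a proportional loss shared by all lamp users would rescale the slope but leave the correlation unchanged. Finally, section 9 does not say that desk time and clothing are the only inputs, and detail could follow in an analysis plan.

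Much of this stands. It limits the size of the problem and rules out treating misclassification as established. It does not remove the gap. The protocol itself names the inputs to the dose, omits lamp output, and plans a daily reading of that output without assigning it to any analysis. Reports and weekly checks do not reach the dose variable either.

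Two further readings are tempting but unsupported:

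- *Controls are credited with a lamp dose because they keep the same diary.* Section 9 speaks of the dose received, and section 7.2 says that only the intervention group gets any noteworthy UVB. Control diaries have other uses: comparing natural UVB and adjusting for desk presence and time outside. One clarifying sentence is enough.
- *The dosimeter already documents every interruption.* Its stated role is checking stability, its time resolution is not given, and it sits at the desk rather than on the person.

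**Conclusion.** The concern holds in a limited form. As defined in section 9, the UVB dose can be misclassified without anyone seeing it, because it assumes full lamp output whenever the participant is at the desk. By section 6.2, a brief interruption can remove up to 38% of a day's dose in the morning or 50% just after 13.00.

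A reader might infer that every interruption costs hours of UVB, or that the dose is in fact misclassified. The documents support neither. The loss depends on clock time: minutes shortly before noon, little late in the afternoon, possibly none overnight. No interruption rate is given. Isolated outages would hardly matter; repeated re-powering by a few of the 14 lamp users would. The correlations rest on the assumed spread of desk time and body surface and on assumed outage patterns.

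Only the exploratory dose model is affected. The primary ANCOVA compares groups by allocation and has no dose term. Nor should the 8.8 nmol/L difference in Table 2 between 0.45 and 0.225 SED (at 10.5% body surface) be read as the effect of outages: it is simulated for a dose halved over the whole eight weeks. This is an inexpensive improvement, not a threat to the main result.

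**What to change.** In section 9, define the daily lamp dose for lamp users as the diary-based dose (desk time × exposed body surface) multiplied by the recorded lamp output relative to the expected full-day output, taken from the desk dosimeter. Use whatever time resolution the dosimeter gives. If morning and afternoon can be separated, apply the ratio within each diary block. If only a daily total exists, use that, and note that it assumes desk time was spread evenly over periods with and without UVB.

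Also:

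- use the diary-only formula on days without dosimeter data, and for the whole period as a sensitivity analysis;
- report, per participant, the number of days with missing or reduced lamp output;
- state that lamp dose is zero for controls;
- reconcile the restart descriptions in section 6.2 and Table 4 for power restored before 8:50 and between 12:00 and 13.00.

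**Cost.** No new measurement is needed. Dosimeter files must be transferred under the participant code, a route that section 7.3 does not yet describe, and there is some extra data handling. One limit remains: the dosimeter records output at the desk, not exposure on the skin, so desk time and clothing must stay in the formula.
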